### Screening

Screening will take place by the potential participant's GP or Mental Health Professional who will be given a flow chart of inclusion criteria. Alternatively, if the participant has been referred by non mental health community/voluntary services he/she will be screened by a member of the research team who will administer the Children's Depression Inventory (CDI).

### Primary outcome measure

#### The Children's Depression Inventory 2(CDI-2) [22]

The CDI-2 consists of 28-items designed to assess depression scores in young people aged 7 to 17. For each item the there are three possible answers; 0 indicating the absence of symptoms, 1 the mild symptoms, and 2 the definite symptoms. The total score ranges from 0 to 54. The CDI is sensitive to changes in depressive symptoms over time and is a useful index of the severity of the depressive syndrome.

### Secondary outcome measures

#### European Quality of Life-5 Dimensions (EQ-5D)

The EQ-5D is a standardised measure of health-related quality of life that provides a simple, generic measure of health for clinical and economic appraisal^. ^It comprises five questions on mobility, self care, pain, usual activities, and psychological status with five possible answers for each item (1 = no problem, 2 = slight problem, 3 = moderate problem, 4 = severe problem, 5 = unable. It is applicable to a wide range of health conditions and treatments; it provides a simple descriptive profile and a single index value for health status.

#### The Client Receipt of Service Inventory (CRSI)

The CSRI is a questionnaire that collects retrospective information on service utilisation, service-related issues and income in a manner commensurate with estimating care package costs.

#### The Borg (RPE) Scale [23]

THE RPE scale is a simple method of rating perceived exertion (RPE) and to gauge a person's level of intensity when exercising. It has an ordinal scale that ranges from 0-16 with verbal anchors allowing the participants to designate their level of intensity more accurately and for answers to be standardized across individuals and tasks.

Heart Rate

Resting Heart Rate

Self Harm

The number of incidents of self harm in the last 3 months

Compliance with intervention

The number of exercise session each participant attends

### Procedure

The intervention group will undertake 12 × 60 minute aerobic exercise sessions, in groups of 5-10, tailored to participants' exercise levels and preferences led by a qualified exercise therapist. The intervention group will also receive psychosocial and motivational support throughout each session to facilitate ongoing participation and enduring change. The motivational coaching will consist of behaviour modification: goal setting, self-monitoring, social support, enhancing self-efficacy and shaping.

Participants will have baseline measures taken at the initial session. Outcome measures will be repeated at post intervention in the final session and at 6 month follow up at a location that suits the participant.

Participants in the intervention group will be invited to participate in focus groups and face-to-face interviews following completion of the exercise programme. These will take place at a location agreed with participants and researchers. It is hoped that these will be conducted at the centres at which the exercise takes place. The data will be recorded on an audio tape with the informed consent from the participants and their legal guardians. The facilitator will also take written notes which will help identify the participants in the recording. Data will be transcribed, coded and analysed for patterns, themes and sub-categories, paying particular attention to outliers and rival explanations given by participants.

The control group will receive usual care throughout the 12 week intervention period. Outcome measures will be taken within the same week as the paired intervention group; at baseline, post intervention (12 weeks later) and at 6 month follow up.

Resource data will be collected for an economic evaluation using the Client Receipt of Service Inventory (CSRI) which is a comprehensive inventory of resource use that has been widely used in economic evaluations of mental health interventions [24]. Resource use will be valued using published, and where appropriate patient reported, unit costs. The primary measure for the cost effectiveness analysis will be the SPPA (with sensitivity analysis covering a range of possible outcomes). Assessing health related quality of life using the EQ-5D will enable a cost utility analysis to be undertaken for the trial period. Using the information on costs and benefits an incremental economic analysis comparing the tailored exercise intervention to treatment as usual will be undertaken to estimate mean cost-effectiveness. To test the robustness of results in the face or any uncertainties, and in order to improve the generalisability of results, sensitivity analysis will be conducted. In addition, uncertainty surrounding the cost-effectiveness of the tailored exercise intervention will be presented graphically using Cost-Effectiveness Acceptability Curves [25]. Should the data be skewed then non-parametric bootstrap analysis using the percentile method confidence interval [26] will be undertaken and incremental net benefits estimated.

The project steering group will be used to undertake an implementation analysis of the project's findings in order to understand knowledge transfer from research to clinical practice in the health service. Such an approach is in line with MRC guidance for developing and evaluating complex interventions [27]. The MRC guidance highlights that clinical ineffectiveness may be a result of an implementation failure; as a result, it calls for multi-level, process evaluations that may go beyond RCTs to understand such failure. In the steering group we intend to elicit from members the issues relating to the uptake of the findings from the proposed study and the barriers we may encounter in doing this. Each member of the group will complete a proforma eliciting a Social Network Analysis of their interactions with other service providers to better understand the concerns of providers not immediately associated with the project.

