### Sample size and justification

128 participants are required in order to have 80% power to detect a difference in mean change of the primary outcome measure. This assumes equal standard deviations of 16 points and using a pre-specified significance level of *p *< 0.05. Assuming 20% attrition rates, it is proposed to recruit 158 participants to the study (79 intervention arm, 79 control arm).

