### Statistical analysis

SPSS V.18 will be used for the analysis of the results. The two groups will be described in terms of their baseline characteristics. Our primary outcome will be the CDI post intervention. A regression model will be used to compare the two groups in terms of the CDI score post intervention conditional on baseline score. No other confounders will be adjusted for unless there appears to be an imbalance at baseline between the two groups on pre-specified covariates that are considered to influence outcome. For secondary outcomes, similar models will be built all conditional on the relevant baseline score in addition to baseline CDI score. Analyses will be intention-to-treat and conducted on a dataset where codes for the two intervention groups are unlabeled. All estimates of effect sizes and numbers needed to treat will be reported with 95% confidence intervals. One of the potential problems with early studies testing a relatively new intervention with a group in whom it is largely untested is that the results may be skewed in a positive direction. To minimise this potential effect, the statistical analyses will be conducted independently of the research team. Qualitative analysis of the focus groups and interviews will be conducted using NVivo 9 in order to code the information and look for relevant trends and themes within the data.

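### Exercise is delivered in groups of 5-10, but the sample size has no design effect and the primary regression has no group term; any positive within-group correlation would make the planned standard error too small

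*Protocol article*

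**What the plan says.** All of this is in the Protocol article.

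- **Procedure, intervention arm.** Participants attend twelve one-hour "aerobic exercise sessions, in groups of 5-10", fitted to each person's level and wishes, with an exercise therapist in charge. Motivational support is given in every session, and its listed techniques are "goal setting, self-monitoring, social support, enhancing self-efficacy and shaping".
- **Procedure, control arm.** "The control group will receive usual care throughout the 12 week intervention period". No treatment groups are described for controls. Their measurements are timed to the same week as those of a paired intervention group.
- **Sample size and justification.** The evaluable target is given in one sentence: "128 participants are required in order to have 80% power to detect a difference in mean change of the primary outcome measure". On variability, the section adds: "This assumes equal standard deviations of 16 points". The significance level is given, and 20% attrition raises the target to 158 (79 per arm). No target difference, ICC, group size or design effect appears.
- **Statistical analysis.** The primary model is described thus: "A regression model will be used to compare the two groups in terms of the CDI score post intervention conditional on baseline score". Other terms enter only if pre-specified covariates look imbalanced at baseline. No exercise-group effect, random effect or robust standard error is mentioned.

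**The concern.** Participants are randomised individually, but those allocated to exercise are then treated together for 12 sessions, with social support among the coaching techniques. Members of one group may therefore end up more alike than members of different groups. Nothing comparable is described for controls, so this is a partially nested design with clustering by delivery in one arm only.

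A regression on arm and baseline that treats every participant as independent ignores this. Under positive correlation it credits the exercise arm with more information than it holds. The error then runs towards intervals that are too narrow and towards false positive findings on the primary outcome. The Statistical analysis section itself worries about results skewed in a positive direction.

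**Working it through.** **Inputs from the protocol:** 128 evaluable (64 per arm), SD 16, 80% power, significance level 0.05, 20% attrition, groups of 5-10.

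**Assumed, because the protocol does not give them:** two-sided test; target difference 8 points (0.5 SD), back-solved; ICC 0.01 to 0.10; group size m of 5, 7.5 or 10 evaluable members.

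**1. Reproducing the plan's figure.** With independent participants, a difference of 8, SD 16 and two-sided 0.05, the noncentral t gives power 0.801 at 64 per arm (0.795 at 63). The normal approximation gives 63 per arm, or 126 in total. A one-sided test would need only 50 per arm, which does not match. For attrition, 126/0.8 = 158 after rounding up and 128/0.8 = 160. So 128 is the plain independent-participant result and 158 is attrition alone. Neither figure leaves room for clustering.

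**2. Adding clustering in the exercise arm only.**

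- Design effect in that arm: DE = 1 + (m - 1) × ICC
- Variance inflation of the difference: (1 + DE)/2
- Power = Φ(0.5 / √((2/64) × inflation) - 1.96)
- Type I error of the unclustered test = 2 × (1 - Φ(1.96/√inflation))

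Example with m = 7.5 and ICC 0.05: DE = 1 + 6.5 × 0.05 = 1.325, and inflation = 2.325/2 = 1.1625. Power = Φ(0.5/√(0.03125 × 1.1625) - 1.96) = 0.746. Type I error = 2 × (1 - Φ(1.96/1.078)) = 0.069.

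The last column replaces the normal approximation by a noncentral t with Satterthwaite degrees of freedom, (v1 + v0)² / (v1²/(k - 1) + v0²/63). Here v1 = 256 × DE/64, v0 = 256/64 and k = 64/m, which is about 6 to 13 groups.

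| ICC | m | Inflation | Type I error, unclustered test | Power, normal | Power, small-sample df |
|---|---|---|---|---|---|
| 0.01 | 5 | 1.020 | 5.2% | 80% | 78% |
| 0.01 | 7.5 | 1.033 | 5.4% | 79% | 76% |
| 0.01 | 10 | 1.045 | 5.5% | 79% | 75% |
| 0.05 | 5 | 1.100 | 6.2% | 77% | 75% |
| 0.05 | 7.5 | 1.163 | 6.9% | 75% | 71% |
| 0.05 | 10 | 1.225 | 7.7% | 72% | 67% |
| 0.10 | 5 | 1.200 | 7.4% | 73% | 71% |
| 0.10 | 7.5 | 1.325 | 8.9% | 69% | 64% |
| 0.10 | 10 | 1.450 | 10.4% | 65% | 58% |

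Without clustering, the same normal approximation gives 81% (0.807). If 5-10 is the size at enrolment and 20% are lost, m is 4 to 8. At ICC 0.05 the type I error is then 5.9% to 7.1% and power (normal) 78% to 74%.

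**3. Checking the type I formula.** A simulation of the ordinary two-sample t-test (8 groups of 8 against 64 unclustered controls, zero mean difference, 40,000 runs) gave 7.3% at ICC 0.05 and 9.1% at ICC 0.10. The formula gives 7.1% and 9.2%.

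**4. Allowing for baseline adjustment.** Assume 16 is the raw SD, the baseline-outcome correlation is 0.5 and the ICC of 0.05 refers to total variance. Residual variance is 256 × (1 - 0.25) = 192 and between-group variance is 0.05 × 256 = 12.8. With m = 7.5, the variance of the difference is (192 + 6.5 × 12.8)/64 + 192/64 = 4.3 + 3.0 = 7.3. The standard error is 2.702, and power is Φ(8/2.702 - 1.96) = 0.84. The unclustered variance would be 6.0, so it is still understated by a factor of 7.3/6.0 = 1.22.

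By the same formula, m = 10 gives 0.82. A correlation of 0.3 at m = 7.5 gives 0.78. At ICC 0.10 and m = 10, power is 0.73 for a correlation of 0.5 and 0.77 for 0.6.

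**The case against.** **The ICC may be close to zero.** This stands as a limit on size. The documents give no ICC, and at 0.01 nothing of consequence happens. Some of the shared influence is also inferred: if one therapist leads every group, the therapist adds no variance between groups, and sessions are tailored to the individual. The plan nonetheless assumes exactly zero without saying so.

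**The type I figures need a particular null.** This also stands. If exercise changes nobody's outcome, delivery in groups adds no correlation. The figures describe a zero average effect that still varies between groups.

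**Power may hold up.** A reader might infer that true power must be below 80%. The documents do not support that. The sample size is framed on mean change, whereas the analysis conditions on baseline, and step 4 shows power anywhere from 0.73 to 0.84 depending on two quantities that the protocol does not give. What fails is the idea that baseline adjustment settles the matter, because the standard error remains too small.

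**The error structure belongs in a statistical analysis plan.** The protocol speaks only of a regression model, which a mixed model or cluster-robust errors could satisfy. But the article itself fixes the basis of the sample size and the terms of the primary model, and limits further adjustment to imbalanced covariates. A group effect added later would alter the stated analysis.

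**Controls may be paired with exercise groups in time.** The Procedure section ties control measurements to the week of a paired intervention group. Cohort or calendar effects shared by both arms would partly cancel in the comparison. This bears on the form of the model and does not remove correlation that arises from shared treatment.

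**Conclusion.** The concern holds in conditional form. Group delivery is explicit, the sample size reproduces as an independent-participant calculation with nothing spare, and the stated model has no term for exercise group. If within-group correlation is positive, the planned standard error is too small and the sample size calculation overstates power on its own terms.

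The size depends on an assumed ICC: negligible at 0.01, and a type I error of about 6-8% at 0.05 and 7-10% at 0.10. Those ranges rest on 64 evaluable per arm and groups of 5-10; the power figures rest also on the back-solved 0.5 SD. The documents do not establish that the ICC is positive or that final power falls short of 80%. It is a point that should be corrected, certain in structure and moderate in likely size.

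**What to change.** **Statistical analysis.** Specify a partially nested mixed model for the primary outcome: post-intervention CDI-2 on arm and baseline CDI-2, a random exercise-group effect in the intervention arm only, residual variances that differ by arm, and small-sample degrees of freedom. State that it uses recorded exercise-group membership. If controls are paired with exercise cohorts in time, consider a cohort term common to both arms.

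**Sample size and justification.** Restate power over an ICC range such as 0.01 to 0.10, giving the target difference, the expected group size and any baseline-outcome correlation relied on.

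**Cost.** A change of wording, plus one data field if group membership is not already held. The confidence interval will be somewhat wider, there will be fewer degrees of freedom with only about 6-13 groups, and the stated power may fall. The change itself requires no extra participants. If the sponsor wished to hold 80% at ICC 0.05 without relying on baseline adjustment, scaling 128 by the inflation factor (normal approximation) and dividing by 0.8 gives 178 to 198 recruited for groups of 5 to 10, against the 158 planned.

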### Randomisation and blinding

Allocated to experimental or control arm will be by computer generated numbers by a researcher not associated with the study. Measurements of baseline, outcome and follow-up measures will be taken by a researcher not associated with the study. Baseline outcome measures will be taken after random allocation. The exercise therapist and focus group facilitator will only know which participants get the exercise intervention.

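### The exercise arm's primary outcome is collected in the last exercise session, while controls are matched only by week, so attendance and setting can bias the comparison

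*Protocol article*

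**What the plan says.** All references are to the protocol article.

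- **Exercise arm (Procedure).** "Outcome measures will be repeated at post intervention in the final session". The same sentence adds the six-month visit, at a place convenient to the participant. Baseline is handled in the same way as the post-intervention visit: "Participants will have baseline measures taken at the initial session".
- **Control arm (Procedure).** "The control group will receive usual care throughout the 12 week intervention period", so controls have no exercise session. Their measurement is fixed by calendar only: "Outcome measures will be taken within the same week as the paired intervention group". No place is named.
- **Who measures (Randomisation and blinding).** "Measurements of baseline, outcome and follow-up measures will be taken by a researcher not associated with the study". That section also puts baseline measurement after allocation.
- **What the measurement feeds (Statistical analysis).** The primary outcome is the post-intervention CDI, compared by a regression conditional on the baseline score. "Analyses will be intention-to-treat", on a dataset with unlabelled group codes.
- **Attendance.** The abstract describes compliance with prescribed exercise programmes as generally low, and the number of sessions attended is listed as an outcome.

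**The concern.** The occasion on which the primary outcome is collected is itself part of the treatment in one arm and not in the other. Three consequences follow if the procedure is carried out as written.

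1. **Missing outcomes may depend on attendance in one arm only.** An exercise participant who has dropped out of the sessions, or misses the twelfth, has no stated route to a post-intervention CDI. Controls face no attendance condition. An analysis plan can model missing values, but it cannot recover scores that the procedure did not set out to collect.
2. **The setting reveals the arm.** Anyone measuring at an exercise session can see the allocation of the person being measured.
3. **The circumstances of answering differ.** Sessions are run in groups of 5-10 with motivational and psychosocial support. Exercisers complete a mood inventory in that company; controls cannot.

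The Statistical analysis section worries that early studies of a new intervention tend to lean positive, and answers with independent analysis on unlabelled codes. That safeguard acts after the data are collected and cannot undo an asymmetry created at collection.

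**Working it through.** **Step 1. Set the rules side by side.**

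| | Exercise arm | Control arm |
|---|---|---|
| Post-intervention occasion | Final exercise session | Same week as the paired exercise group |
| Place | The session | Not stated; cannot be an exercise session of their own |
| Attendance needed, as written | Yes | No |
| Six months | A place convenient to the participant | No place stated |
| Assessor | Outside researcher, not stated to be masked | Same |

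**Step 2. The plan's own scale.** The Sample size section gives 128 evaluable participants (64 per arm), SD 16, 80% power and significance level 0.05. It gives no target difference, so I back-solve it, assuming a two-sided test: 16 × √(2/64) × (1.960 + 0.842) = 7.92, about 8 points. Forward, a t-test at 8 points needs 63.8, so 64 per arm, which reproduces 128. The 8 points is used below only as a yardstick.

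**Step 3. Bias in a complete-case comparison.** Let p be the share of an arm without a post-intervention score, and g the mean CDI of those missing minus the mean of those measured (higher is worse). The observed arm mean is too low by p × g. The bias in the difference, in favour of exercise, is

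p(exercise) × g(exercise) − p(control) × g(control).

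The documents give neither p by arm nor g, so the values here are assumptions. With control loss unrelated to outcome, g(control) = 0:

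| Exercise arm absent | Gap 3 points | Gap 5 points |
|---|---|---|
| 20% | 0.2 × 3 = 0.6 | 0.2 × 5 = 1.0 |
| 30% | 0.3 × 3 = 0.9 | 0.3 × 5 = 1.5 |

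Against the implied 8 points this is 0.6/8 = 7.5% to 1.5/8 = 18.75%.

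**Step 4. How far this depends on the controls.** If 20% of controls are also lost with a gap of 3 points, 0.2 × 3 = 0.6 is subtracted. The range becomes 0 to 0.9 points, so equally informative control loss can remove the bias.

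**Step 5. Effect on the test.** With 79 randomised per arm, SD 16, 20% of controls lost at random and no baseline adjustment, the true type I error of a nominal 5% test is:

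| Exercise arm absent | Gap | Bias | Type I error |
|---|---|---|---|
| 20% | 4 | 0.8 | 5.9% |
| 30% | 4 | 1.2 | 6.9% |
| 20% | 8 | 1.6 | 8.7% |
| 40% | 8 | 3.2 | 18.0% |

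For a true 8-point effect, power falls from 79.6% with 20% missing in both arms to 73.2% with 40% missing in the exercise arm and 20% in controls. The main exposure is bias rather than lost power.

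**The case against.** The best defence is that the section says where the visit is normally held, not that absentees are abandoned. Procedures for chasing missed visits are detail that an article commonly leaves to the full protocol. This stands in part: another route is not ruled out, so the loss of non-attenders is a risk and not a stated fact. What is stated, however, is a place and occasion that only one arm has. One could read the flexible location as covering the post-intervention visit too, but the words placing that visit in the final session would remain.

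Four stronger readings are tempting and are not supported.

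- **That independent assessment is defeated.** The article promises collection independent of the research team. It does not promise an assessor masked to arm, and an outside researcher at a session is still independent. Participants also know their own arm, so masking the assessor would not remove their expectations.
- **That intention-to-treat is contradicted.** That commitment concerns how participants are analysed. Incomplete collection is a missing-data risk that strains the aim without contradicting it.
- **That resting heart rate is distorted by exercise.** Nothing says whether it is taken before or after exertion.
- **That non-attenders are shown to be many and worse off.** The low compliance cited concerns prescribed programmes, and preferred intensity is proposed to reduce attrition. The only planning figure is 20% attrition for the whole trial.

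Two technical objections also stand. Adjustment for baseline CDI would shrink any gap explained by baseline severity. And because baseline is also taken at a session, a stable setting effect could partly cancel in the exercise arm.

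**Conclusion.** The point holds as a badly fixed measurement rule that should be changed. Followed as written, it ties the primary CDI in the exercise arm to attendance at the last session and to the treatment setting, while controls are matched only by week. The direction is towards exercise if non-attenders do worse and control losses are not similarly informative; the documents establish neither condition. The size is unknown. The 0.6-1.5 points is an illustration that rests on assumed absence of 20-30%, an assumed gap of 3-5 points, control loss unrelated to outcome and no baseline adjustment. A reader might infer that the trial will compare only attending exercisers with all controls; the text does not go that far, because a route for absentees may exist elsewhere. The asymmetry in place and occasion does not depend on any of these figures.

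**What to change.** Reword the Procedure section along these lines: *Post-intervention measures are taken for all randomised participants in the same fixed window at about week 12, whether or not they attended the sessions. They are taken outside any exercise session, in the same kind of setting in both arms, by the independent researcher, who where feasible is not told the allocation. The participant may choose a convenient location, as at six months. Baseline measures are likewise taken outside the exercise session.*

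The baseline sentence is needed because moving only the later visit would create a new mismatch of setting within the exercise arm.

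Cost: some separate appointments for exercise-arm participants at baseline and week 12, and the possible loss of a few attenders who would have completed the measures at the session. Keeping the assessor unaware of allocation goes beyond what the article now promises and needs some organisation. The sample size and the intervention do not change.

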**Methods/Design:**

A sequential mixed methods design will be utilised to assess the effectiveness of an individually tailored exercise programme on the mental health outcomes of young people with depression. The mixed methods design incorporates a Randomised Controlled Trial (RCT), focus groups and interviews and an economic evaluation. *Participants: *158 young people (14-17 years) recruited from primary care and voluntary services randomly allocated to either the intervention group or control group. *Intervention group*: Participants will undertake a 12 week exercise programme of 12 × 60 minutes of preferred intensity aerobic exercise receiving motivational coaching and support throughout. Participants will also be invited to attend focus groups and 1-1 interviews following completion of the exercise programme to illicit potential barriers facilitators to participation. *Control group*: Participants will receive treatment as usual. *Primary Outcome measure*: Depression using the Children's Depression Inventory 2 (CDI-2). *Secondary Outcome measures*: Quality of Life (EQ-5D), physical fitness (Borg RPE scale, heart rate), incidents of self-harm, treatment received and compliance with treatment, and the cost effectiveness of the intervention. Outcome measures will be taken at baseline, post intervention and 6 month follow up.

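### The cost-effectiveness analysis takes as its primary effect measure the SPPA, which is undefined and not among the outcomes the article lists as collected, so that analysis cannot be run from the listed data

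*Protocol article*

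**What the plan says.** The economic evaluation is described in the Procedure section of the Protocol article. Costs come from the service-use inventory, and the effect measure is fixed in one sentence: "The primary measure for the cost effectiveness analysis will be the SPPA". A parenthesis in that sentence adds sensitivity analysis over several outcomes. The paragraph then plans a cost-utility analysis on the EQ-5D, an incremental comparison with usual treatment, acceptability curves and, if the data are skewed, bootstrap intervals and net benefits.

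The outcomes are set out in three other places:

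- The abstract gives the primary outcome as "Depression using the Children's Depression Inventory 2 (CDI-2") and the secondary outcomes as "Quality of Life (EQ-5D), physical fitness (Borg RPE scale, heart rate), incidents of self-harm, treatment received and compliance with treatment", together with cost effectiveness itself.
- The outcome sections describe the CDI-2, EQ-5D, service-use inventory, Borg RPE, resting heart rate, self-harm and session attendance.
- The Statistical analysis section confirms: "Our primary outcome will be the CDI post intervention".

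Cost effectiveness is the third of three numbered objectives. It also forms part of the hypothesis and is one of the three parts of the design.

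**The concern.** A cost-effectiveness ratio, a net benefit or an acceptability curve needs an effect measured in both arms on the chosen scale. Here the scale labelled primary is a term that the article neither explains nor lists as collected. Taken literally, the analysis has costs but no listed effect.

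If the sentence is left as it stands, someone will have to decide later what it meant. If that happens after the results are known, the choice could fall on CDI-2, self-harm or another measure, and these need not give the same economic answer. The Statistical analysis section itself worries that early trials of a new intervention may lean in a favourable direction. An effect measure that is in practice open leaves room for that.

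**Working it through.** There is no figure to reproduce, so the check is a comparison of the article's sections.

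**Step 1: where SPPA appears.**

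| Place in the article | SPPA mentioned? |
|---|---|
| Abstract, Methods/Design (outcome list) | No |
| Primary outcome measure | No, CDI-2 only |
| Secondary outcome measures | No |
| Procedure, sessions and assessments | No, refers to outcome measures in general |
| Procedure, economic evaluation | Yes, once |
| Statistical analysis | No |
| Abbreviations | No, although CDI, CSRI, EQ-5D and RPE are listed |

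**Step 2: could a listed measure be the SPPA under another name?** Each one is described, and none carries that name.

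| Listed measure | What the article says it is | Possible role in the economic evaluation |
|---|---|---|
| CDI-2 | "The CDI-2 consists of 28-items designed to assess depression scores" | Effect; usable but not specified |
| EQ-5D | "The EQ-5D is a standardised measure of health-related quality of life" | Effect in the cost-utility analysis, as planned |
| Service-use inventory | "The CSRI is a questionnaire that collects retrospective information on service utilisation, service-related issues and income" | Costs, not effects |
| Borg RPE | Perceived exertion during exercise | Not named for this purpose |
| Resting heart rate | Fitness measure | Not named for this purpose |
| Self-harm | Incidents over the past three months | Effect; usable but not specified |
| Sessions attended | Compliance with the exercise programme | Not a between-arm effect, since controls have no sessions |

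Of the seven listed measures, none is the SPPA.

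**Step 3: which analyses are affected.** The economic paragraph names two analyses by effect measure:

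- Cost-effectiveness on the SPPA: no listed effect data, so it cannot be carried out from what the article lists.
- Cost-utility on the EQ-5D: the measure is listed, and outcomes are taken in both arms at baseline, after the intervention and at six months. This can be carried out.

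One of the two is blocked, and it is the one whose measure is labelled primary.

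**Step 4: does the parenthesis about sensitivity analysis supply a substitute?** No. It refers to several possible outcomes without naming any, and it concerns sensitivity analysis around the SPPA result rather than the main analysis.

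**The case against.** The strongest reply is that this is a condensed journal article. The SPPA may be an instrument that the full protocol collects and the article's outcome list left out, or it may be a leftover label where another outcome was meant. The text cannot separate the two, and this limit stands: the article shows only that the SPPA is not listed as collected. A reader might infer that the trial does not collect it and that all its effect data are absent. The article does not establish that.

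A reader might also infer that only the EQ-5D analysis can be computed, or that the cost-effectiveness objective cannot be met. Neither follows. CDI-2 is scheduled in both arms, so a cost per CDI-2 point is computable. The objective names no measure, and the EQ-5D analysis is already planned, so relying on it would not be a post hoc retreat.

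Nor is it an error in itself that the economic measure differs from the clinical primary outcome. Nothing in the article requires them to match. The missing abbreviation is editorial and carries little weight alone. The lack of a visit for the SPPA adds little too, because the Procedure section schedules outcome measures without naming instruments by visit.

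What the reply does not remove is the contradiction. The article does not leave the effect measure to a fuller document. It fixes one, calls it primary, and omits it from its own outcome lists in both the abstract and the body. A fuller document could add detail, but the economic paragraph and the outcome lists would still disagree.

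**Conclusion.** The point holds in a limited form. The named primary effect measure for the cost-effectiveness analysis is undefined and is not among the seven measures listed, so that analysis cannot be carried out from the listed data. The EQ-5D cost-utility analysis is unaffected, and a CDI-2 analysis would be possible but is not the one specified. The clinical primary outcome, its regression analysis and the sample size are not touched.

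The conclusion assumes that the article's outcome lists are meant to be complete. If the full protocol collects the SPPA, the defect lies in the article's outcome list and in the missing definition, and the data may exist. The correction is needed on either reading, because the sections disagree on a stated objective.

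**What to change.** Before any outcome data are seen, reconcile the economic paragraph in Procedure with the outcome lists in the abstract and the outcome sections, in one of two ways:

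1. Name a collected outcome as the effect measure. The most natural choice is the CDI-2 total score, the trial's primary outcome, expressed as cost per point of improvement. State the time point, since outcomes are taken both after the intervention and at six months. Keep the EQ-5D cost-utility analysis as planned.
2. If the SPPA is truly intended and is collected under the full protocol, define it and add it to the outcome list and the assessment schedule.

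The first option costs one amended sentence and needs no new data. The second costs a definition and two list entries, provided that the instrument has been given from baseline. If it has not, baseline values cannot be recovered for participants already enrolled, and the first option is the practical one.
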